### Outcomes:

The primary outcome is the composite of ischaemic stroke and other thromboembolic events, or the occurrence of MB events defined according to the ISTH criteria (described in detail in Section D). Secondary outcomes will include CRNMB events that did not satisfy the ISTH criteria and led to hospitalization, medical or surgical treatment, or led to discontinuation of OACs. All outcomes will be identified over the course of follow-up through the identification of corresponding Read codes in patients’ records. For bleeding events since CPRD does not state the number of transfused blood units, any need for blood transfusion along with a Read code for bleeding will be classified as a MB event. Stroke or bleeding events will be identified through Read codes in patients primary care records and through linkage to inpatient HES ICD-10 codes in case of hospitalization secondary to stroke or bleeding. ONS mortality data will be used to ascertain specific causes of death (i.e. bleeding related, cardiovascular, or all-cause death) according

ICD-10 codes. All codes relevant to these outcomes are listed in Appendix 3.

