**Methods and Data analysis:**

The study comprises of three phases; first an epidemiological study that aims to delineate incidence of NVAF from the CPRD GOLD and Aurum databases between 2009 and 2019. Prescribing of OACs will be assessed for all patients with NVAF and in a sub-group with cancer diagnosis and relevant data will be extracted to identify potential predictors of OACs prescribing and further assessment using multivariable logistic-regression modelling. The second phase will be a comparative cohort study of incident NVAF patients who were classified as "OAC not prescribed" in phase one, by using a propensity score matching method to match each patient not prescribed OACs to up to 5 comparable patients treated with OACs. Then we aim to compare stroke, bleeding, and all-cause mortality associated with OACs prescribing versus no OACs. The third phase will focus on patients who developed major bleeding events in phase two while taking OACs. We aim to explore the variability of OACs prescribing after bleeding across patient groups and the different predictors for OACs resumption. We will explore the rate of bleeding reoccurrence, stroke, and mortality, and how they relate to OACs prescribing and timing of restarting OACs. We will assess and compare patients' risk for stroke and bleeding reoccurrence after the bleeding event using different risk-assessment scores.

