## Outcomes to be measured

Throughout the different phases of this project we aim to explore the following outcomes:

- Phase 1 – The primary outcome is the prescription of OAC drugs including; vitamin K antagonists (VKAs) (acenocoumarol, phenindione or warfarin), or non-vitamin K oral anticoagulants (NOACs) (dabigatran, rivaroxaban, apixaban, or edoxaban).
- Phase 2 - The primary outcome is ischaemic stroke and other thromboembolic events, or the occurrence of major bleeding (MB) defined according to the International Society on Thrombosis and Haemostasis (ISTH) criteria as (1) clinically overt bleeding accompanied by a drop-in haemoglobin level of least 2 g/dl and/or (2) transfusion of at least 2 units of packed red cells, occurring at a critical site (i.e., intracranial, intraspinal, intraocular, pericardial, intra-articular, intramuscular, and retroperitoneal) and/or (3) fatal bleeding. Secondary outcomes will include clinically relevant non major bleeding (CRNMB) that did not satisfy the ISTH criteria and led to hospitalization, medical or surgical treatment, or led to discontinuation of OACs.
- Phase 3 – The primary outcomes include the reoccurrence of MB events or CRNMB for patients who did or did not continue on OACs, the rate of stroke and other thromboembolic events, cardiovascular related mortality, and all-cause mortality. The secondary outcome is the prescription of any OACs after the occurrence of the MB events. We aim to explore the timing of reinitiating OACs from the indexed MB event and whether patients have continued the same OAC before the index haemorrhage event, were switched to another OACs or received lone antiplatelet therapy.

All outcomes will be identified over the course of follow-up through the identification of corresponding Read/SNOWMED codes in patients' electronic health records. Hospitalization secondary to stroke or bleeding are to be identified through linkage to HES APC using the 10th revision of the International Classification of Diseases (ICD-10). ONS mortality data will be used to ascertain specific causes of death (i.e. bleeding related, cardiovascular, or all-cause death) according to ICD-10 codes.

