### Specific aims:

1. To determine the incidence of NVAF diagnosis in England from the year 2009 to 2019.
2. To determine the proportions of patients with NVAF and those with NVAF and cancer who were prescribed OACs, antiplatelet alone or no treatment.
3. To examine the temporal trends of prescribing different types of OACs (i.e. VKAs and NOACs), and assess the factors associated with not prescribing OACs including patient demographics, socioeconomic status, history of cancer and other comorbidities, stroke and bleeding risk.
4. To assess the effect of OACs prescribing vs. no OACs on the clinical outcomes (stroke, bleeding, and death) in a comparative cohort of NVAF patients eligible for anticoagulation after controlling for patients' comorbid conditions, frailty, age, and antiplatelets use.
5. To assess the rate of clinical outcomes (i.e. bleeding recurrence, stroke, and mortality) after MB events and how they relate to OACs resumption and the timing of restarting OACs after the MB event.
6. To explore the variability across patient groups regarding OACs resumption after MB events and whether patients have continued on the same OAC before the MB event, switched to another OACs or received lone antiplatelet therapy.
7. To assess and compare patients' risk for stroke and bleeding recurrence using HAS-BLED, CHA2DS2-VASC, HEMORR?HAGES and GARFIELD-AF risk assessment scores, at the time of the indexed major bleeding event.

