### **Sample size considerations**

Due to the comparative nature of the second phase of this study, a sample size calculation was undertaken to provide an estimate of the number of cases needed for the second phase of this project (the comparative cohort), and to detect a difference in the major outcomes of interest (ischemic stroke, mortality, or bleeding) between OACs exposed and not exposed NVAF patients. Power calculations were based on stroke within a year of NVAF diagnosis since it is our primary outcome of interest. An Earlier study showed a yearly stroke incidence ranging of 8% with no OACs and 2.8% in patients treated with warfarin. We have assumed an alpha level (two-tailed) of 0.05, a beta of 0.2 (80% power), and a ratio of 5:1 for the OACs exposed-to-unexposed ratios in the matched cohort to detect a relative risk of 2.8 for the dichotomous endpoint (i.e. stroke). This would require a minimum sample number of 970 of patients in OACs treated patients and 194 patients in OACs unexposed patients, giving a total of 1164 patients. Thus, we estimate to have many times the needed numbers in the two databases.

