2. Phase 2 – Comparative study: For comparison of demographic variables and comorbidities among OACs treated and not treated individuals, independent sample t tests will be used for numeric variables, while Chi squared  $\chi^2$  tests or Fisher exact tests will be used for categorical variables. To control for imbalances in patient characteristics between cohorts, we will calculate an exposure-specific propensity score as the predicted probability of receiving OACs conditional upon individuals baseline covariate (as described in section M) using logistic regression models. Then we will consider applying propensity score matching methods to match each OACs unexposed controls to up to 5 NVAF OACs exposed cases using a calliper of 0.2 standard deviation (SD) of the propensity score logit. After matching, Cox regression will be used to compute hazard ratios (HRs) of the outcomes of interest, comparing exposure to OACs versus no OACs. Initially crude HRs will be obtained, then stratified by type of OACs (i.e., VKAs and NOACs) and adjusted for age, and other important covariates described in section N. In this phase immortal time bias would occur due to the definition of exposure, where in the time from AF diagnosis till receipt of OACs those in the “OACs prescribed group” cannot have the outcome by design, otherwise they would have been classified as non OAC users. To avoid the problem of immortal time bias, we will consider using time-varying exposures, where in a survival analysis, the time period previous to the index date of OACs initiation is reclassified as nonuser for those in the “OACs prescribed group”.

3. Phase 3 – Major bleeding events cohort: At first, we will use descriptive statistics to present the overall characteristics of this cohort who have experienced major bleeding events while taking OACs. After that patients will be divided to 2 groups one for the patients who resumed anticoagulation after the index major bleeding event and the other for the group who remained OACs free and will compare the patient characteristics between the two groups using Chi squared  $\chi^2$  tests, Fisher's exact tests, and analysis of variance, as appropriate. Survival (time-to-event) models will be constructed to compare the time between the indexed major bleeding to the earliest event of stroke, bleeding, or all-cause mortality considering if patients were restarted on OACs or not. In Cox models we will control for age, time to OACs resumption, CHA2DS2-VASc

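### The Phase 2 primary outcome is defined inconsistently, and its most natural reading pools an expected benefit with an expected harm; mortality is unranked, and the Phase 3 model does not match its outcome list

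*Protocol*

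**What the plan says.** **Phase 2 primary outcome.** The protocol describes it in three ways:

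- *Exposures, outcomes and covariates*, Phase 2 Outcomes: "The primary outcome is the composite of ischaemic stroke and other thromboembolic events, or the occurrence of MB events".
- *Outcomes to be measured*: "The primary outcome is ischaemic stroke and other thromboembolic events, or the occurrence of major bleeding (MB"), the same pair without the word composite.
- *Sample size considerations*: "Power calculations were based on stroke within a year of NVAF diagnosis since it is our primary outcome of interest".

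**Mortality in Phase 2.** The technical summary says "Then we aim to compare stroke, bleeding, and all-cause mortality associated with OACs prescribing versus no OACs". Specific aim 4, *Sample size considerations* and *Selection of comparison groups/controls* also name death or mortality. The Phase 2 Outcomes paragraph gives a data source for deaths, but the only secondary outcome it lists is non-major bleeding: "Secondary outcomes will include CRNMB events that did not satisfy the ISTH criteria".

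**Phase 3.** Both outcome sections list recurrent bleeding, stroke/thromboembolism and mortality as primary outcomes, in the plural. The analysis section plans survival models "to compare the time between the indexed major bleeding to the earliest event of stroke, bleeding, or all-cause mortality", and *Plan for addressing confounding* repeats the earliest-event idea.

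**The concern.** *Study type* calls Phases 2 and 3 hypothesis-testing, so a reader must be able to tell which outcome is tested. In Phase 2 the answer depends on the section consulted.

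If the pooled version is followed, it suits the question poorly. *Study background* treats stroke prevention and bleeding as opposing considerations in the decision to prescribe, and wants to identify patients who gain from OACs without bleeding. The relative risk of an outcome that counts both depends on the local mix of strokes and bleeds. It can sit near 1 while both components change substantially, and it cannot show who benefits.

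The Phase 3 analysis raises a related problem. Aim 5 asks for the rates of re-bleeding, stroke and death after a major bleed. In a single time-to-earliest-event model, a stroke that follows a re-bleed is not counted.

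**Working it through.** **Inputs from the protocol** (*Sample size considerations*, *Feasibility counts*): one-year stroke risk 8% without OACs and 2.8% with warfarin; two-sided 5% level; 80% power; 5 exposed per unexposed patient; stated minimum 194 unexposed and 970 exposed; about 14,000 untreated patients expected.

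**Assumed, because the protocol gives no bleeding rate:** untreated major bleeding b = 1–5% per year; bleeding relative risk r = 1.5–4 with OACs.

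**Step 1: the protocol's own figure.** For p1 (unexposed), p2 (exposed), k = 5 and p̄ = (p1 + k·p2)/(1 + k), the pooled two-proportion formula is

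n(unexposed) = [1.96·√((1 + 1/k)·p̄(1 − p̄)) + 0.842·√(p1(1 − p1) + p2(1 − p2)/k)]² / (p1 − p2)²

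With 8% and 2.8%, p̄ = 0.0367 and n = (0.4035 + 0.2366)² / 0.052² = 151.5, so 152 unexposed and 760 exposed (174 and 870 with a continuity correction). The stated 194 does not reproduce as labelled. It appears only if the two risks are swapped between the small and the large group (194.4). This errs on the safe side: 194 and 970 give 87.3% power for stroke.

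**Step 2: pooled relative risk.** Adding the component risks (a first-order approximation that ignores patients with both events):

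pooled RR = (0.028 + r·b) / (0.08 + b)

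| Untreated bleeding | r = 1.5 | 2 | 2.5 | 3 | 4 |
|---|---|---|---|---|---|
| 1% | 0.48 | 0.53 | 0.59 | 0.64 | 0.76 |
| 2% | 0.58 | 0.68 | 0.78 | 0.88 | 1.08 |
| 3% | 0.66 | 0.80 | 0.94 | 1.07 | 1.35 |
| 4% | 0.73 | 0.90 | 1.07 | 1.23 | 1.57 |
| 5% | 0.79 | 0.98 | 1.18 | 1.37 | 1.75 |

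Stroke alone has RR = 0.028/0.08 = 0.35, a 65% reduction, in every cell.

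**Step 3: exact cancellation.** Setting the pooled RR to 1 gives r = (0.08 + b − 0.028)/b = 1 + 0.052/b. For b = 1, 2, 3, 4 and 5% this is 6.2, 3.6, 2.7, 2.3 and 2.0.

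**Step 4: numbers needed for the pooled outcome** (formula of Step 1):

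| Bleeding assumption | Unexposed v exposed | Pooled RR | Unexposed needed |
|---|---|---|---|
| 1%, r = 1.5 | 9.0% v 4.3% | 0.48 | 238 |
| 2%, r = 2 | 10.0% v 6.8% | 0.68 | 672 |
| 4%, r = 2 | 12.0% v 10.8% | 0.90 | 6,524 |
| 3%, r = 2.5 | 11.0% v 10.3% | 0.94 | 18,148 |
| 5%, r = 2 | 13.0% v 12.8% | 0.98 | 264,101 |

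The first three fall within the 14,000 expected; the last two do not. The 14,000 derives from a count in CPRD GOLD, so Aurum would add to it, while matching may remove some patients.

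**The case against.** **The pooled reading is not the only one.** In the Phase 3 outcomes, the word composite covers stroke and other thromboembolic events only, so the Phase 2 sentence could mean two outcomes: that composite, and major bleeding. The technical summary, aim 4 and the comparison-groups section name stroke, bleeding and death individually, and the Phase 2 analysis plans hazard ratios for outcomes in the plural. The components would then probably be reported anyway. This stands, and it is why the point is about inconsistency. It does not settle the matter: the sentence is singular, joins the parts with *or*, and nowhere makes each part primary in its own right.

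**A reader might infer that mortality is missing from Phase 2.** The documents do not support that. Several sections name it as an outcome, and the Phase 2 Outcomes paragraph supplies its source: "ONS mortality data will be used to ascertain specific causes of death (i.e. bleeding related, cardiovascular, or all-cause death"). It lacks only a rank.

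**A reader might infer that the pooled result will be null.** That does not follow either. With the protocol's stroke figures and bleeding that doubles from 1–2%, the pooled RR is 0.53–0.68 and remains detectable. Cancellation needs more frequent bleeding, a larger bleeding effect, or a lower stroke risk than the protocol assumes.

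**A reader might infer that Phase 2 discards strokes after a bleed.** No first-event rule is stated for Phase 2, and strokes after a major bleed in exposed patients are a Phase 3 outcome. The earliest-event criticism applies to Phase 3 only. Even there, the phrase might mean the first event of each type, but the text does not say so.

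**Conclusion.** The point holds as an inconsistency in the primary outcome that should be settled before analysis. If separate outcomes were intended, the Phase 2 wording is wrong. If pooling was intended, the outcome mixes effects that the protocol itself sets against each other.

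Its size rests on assumed bleeding rates and on adding component risks without overlap. Over the assumed range the pooled RR can lie well on either side of 1, so masking is a real possibility and not a certainty. The protocol's assurance that the databases hold many times the patients required has been shown for stroke and for no other version of the primary outcome. The mismatch in the stated 194 and 970 is a side matter without practical effect, given the expected cohort.

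Two smaller defects also stand: all-cause mortality is an aim without a place in the Phase 2 hierarchy, and the Phase 3 earliest-event analysis does not correspond to the separate primary outcomes listed for that phase.

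**What to change.** - **Phase 2:** name stroke/thromboembolism and major bleeding as separate co-primary outcomes, or stroke/thromboembolism as primary and major bleeding as the safety outcome. Give each its own Cox model. Label any pooled measure a secondary net-clinical-benefit outcome.
- **Mortality:** assign all-cause mortality a rank in the Phase 2 list.
- **Phase 3:** model each listed outcome separately, and keep the earliest-event analysis as secondary at most.
- **Consistency:** align *Outcomes to be measured*, *Sample size considerations*, the Phase 2 and Phase 3 Outcomes paragraphs, *Data/statistical analysis* and *Plan for addressing confounding*.

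The cost is rewording and a few additional models. Co-primary outcomes may call for a stated split of the significance level, a negligible loss with about 14,000 unexposed patients expected.

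### The Phase 2 primary outcome is stated inconsistently: stroke alone where the study is sized, stroke/thromboembolism or major bleeding where outcomes are defined, with wording that allows one pooled endpoint

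*Protocol*

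**What the plan says.** Three sections of the protocol state the Phase 2 primary outcome, each differently.

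- **Outcomes to be measured, Phase 2:** "The primary outcome is ischaemic stroke and other thromboembolic events, or the occurrence of major bleeding". The outcome is singular, the two parts are joined by an 'or', and the word composite is absent.
- **Exposures, outcomes and covariates, Phase 2, Outcomes:** "The primary outcome is the composite of ischaemic stroke and other thromboembolic events, or the occurrence of MB events". This is the same pair, again singular, now with the word composite.
- **Sample size considerations:** "Power calculations were based on stroke within a year of NVAF diagnosis since it is our primary outcome of interest". Only stroke is sized, from a "yearly stroke incidence ranging of 8% with no OACs and 2.8% in patients treated with warfarin". The same section also says the calculation serves stroke, mortality and bleeding.

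Other sections give a third list. The Technical Summary says: "Then we aim to compare stroke, bleeding, and all-cause mortality associated with OACs prescribing versus no OACs". Specific aim 4 and the section on selection of comparison groups also name stroke, bleeding and death. In both Phase 2 outcome lists the only secondary outcome is clinically relevant non-major bleeding. All-cause death appears in the Phase 2 outcomes paragraph only as something the ONS data will ascertain.

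**The concern.** The Study type section calls Phase 2 hypothesis testing, so a reader should be able to say which hazard ratio is the primary test. From this text that is not possible. The sample size section contradicts the two outcome definitions on any reading, because it names stroke alone and they include MB.

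The wording also leaves open a pooled stroke-or-MB endpoint. The Study background describes OAC prescribing as a trade-off between stroke reduction and potential bleeding, so the two parts are expected to move in opposite directions. A pooled hazard ratio would weight a benefit against a harm by how often each event occurs in the cohort. It could move toward or past 1 with baseline risk alone, while the effects on stroke and on bleeding stayed the same. The stated power was calculated for stroke and would not carry over to such an endpoint.

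**Working it through.** **1. The protocol's own sample size.** Inputs from Sample size considerations: 8% without OACs, 2.8% with warfarin, two-sided alpha 0.05, 80% power, five exposed per unexposed. Stated result: 194 unexposed and 970 exposed, 1,164 in total.

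Two-proportion formula with pooled variance under the null, n being the unexposed group:

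n = [1.96 × √(p̄(1−p̄)(1+1/5)) + 0.842 × √(0.08×0.92 + 0.028×0.972/5)]² / 0.052², with p̄ = (0.08 + 5×0.028)/6 = 0.0367.

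This gives 152 unexposed and 760 exposed (912 in total). The protocol's 194 appears if the ratio is reversed, with five unexposed per exposed: n = 194.4. As labelled, 194 and 970 give 87.3% power for stroke. The stated number is therefore conservative, and it applies to stroke only.

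**2. A pooled endpoint, if that is what is meant.** Let s0 and b0 be the yearly stroke and MB rates without OACs. Keep the protocol's stroke ratio, 2.8/8 = 0.35. The protocol gives no MB rate and no OAC effect on MB. I assume b0 of 1.5% to 3% and a doubling.

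Pooled ratio = (0.35 × s0 + 2 × b0) / (s0 + b0)

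| s0 | b0 = 1.5% | b0 = 3% |
|---|---|---|
| 8% (protocol) | (2.8+3)/9.5 = 0.61 | (2.8+6)/11 = 0.80 |
| 4% (assumed) | (1.4+3)/5.5 = 0.80 | (1.4+6)/7 = 1.06 |
| 2% (assumed) | (0.7+3)/3.5 = 1.06 | (0.7+6)/5 = 1.34 |

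The stroke ratio (0.35) and the bleeding ratio (2.0) are the same in every cell. On the hazard scale the first row is 0.60 and 0.79.

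**3. Where the effects cancel.** With a doubling, the ratio is 1 when 0.65 × s0 = b0. That is s0 = 1.5/0.65 = 2.3% or s0 = 3/0.65 = 4.6%. At the protocol's stroke rates the MB excess would have to equal 8 − 2.8 = 5.2 percentage points (about 5.5 per 100 person-years on the hazard scale). For example, MB would have to rise from 2% to 7.2%, roughly 3.7-fold in hazard.

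**4. Power for a pooled endpoint.** Protocol stroke rates, MB doubled, hazards added:

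| b0 | Pooled HR | Power at 194/970 |
|---|---|---|
| 1% | 0.52 | 62% |
| 2% | 0.67 | 36% |
| 3% | 0.79 | 17% |
| 4% | 0.90 | 7% |

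Feasibility counts expects about 14,000 untreated patients. If all were matched five to one, power would be at least 96% in each of these four cases.

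**The case against.** The strongest reply is that the protocol may not intend pooling at all. In the Phase 2 paragraph the word composite can cover stroke and thromboembolism only, with MB as a second primary outcome. The Phase 3 outcomes use the word in that narrower way and list recurrent bleeding separately, and Outcomes to be measured omits it. Aim 4 and the Technical Summary list the outcomes one by one. The Phase 2 analysis plans hazard ratios for outcomes in the plural, and no Phase 2 analysis text describes a pooled model. The component effects would therefore probably be reported anyway.

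Most of this stands. A reader might infer that the protocol commits to one pooled primary endpoint whose hazard ratio will sit near 1 and hide both effects. The documents do not support that: pooling is one reading among two, and at the protocol's stroke rates with the assumed doubling the ratio still shows a clear benefit. Values near 1 need stroke or bleeding rates that the protocol does not give. Nor can mortality be called absent from Phase 2; it is compared but not ranked.

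The reply does not remove the inconsistency. Both definitions use the singular for Phase 2, where Phase 3 speaks of primary outcomes, and the Phase 3 survival analysis is timed to the earliest of stroke, bleeding or death. Pooling is thus a natural reading. On the narrower one there are two primary outcomes in one section, one in another, and no statement of which is the primary test.

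**Conclusion.** The concern holds as an inconsistent and unfixed primary outcome for a hypothesis-testing phase. The conflict between the sample size section and the two outcome definitions needs no assumption. Neither does the unranked status of all-cause mortality.

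The size of the pooling problem is conditional on the pooled reading and on assumed bleeding rates. With the protocol's stroke rates and MB doubled from 1.5% to 3% per year, the estimate moves from 0.35 to about 0.61 to 0.80. Cancellation near 1 needs stroke rates of about 2% to 4% per year, or a bleeding excess well above a doubling at these MB rates.

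A reader might also infer that Phase 2 is underpowered. At the stated minimum it would be for a pooled endpoint, but at the expected cohort size, before matching losses, it would not be in the doubling cases that use the protocol's stroke rates. What is at stake is how the primary result is interpreted and which test it is.

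**What to change.** Make Outcomes to be measured, Sample size considerations and the Phase 2 outcomes paragraph agree. Either of two forms would do:

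- Stroke/thromboembolism is the primary outcome, in line with the sizing on stroke, and MB is analysed separately in its own time-to-event model.
- Stroke/thromboembolism and MB are explicit co-primary outcomes, each with its own model, and a multiplicity rule says whether one or both must be significant and at what level.

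In either form, list all-cause mortality as a named Phase 2 outcome with a stated rank. Keep any stroke-or-MB composite only as a labelled secondary net-outcome summary, shown beside its components.

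The cost is protocol wording. The same events are already to be extracted from primary care, HES and ONS records, and the expected cohort far exceeds the stated minimum.

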**Outcomes:**

The primary outcomes will be the prescription of OACs either VKA or NOACs, product codes for OACs are described in (Appendix 2). Status of anticoagulation therapy will be classified as either OAC prescribed or OAC not prescribed. OAC prescription will be defined as the presence of any OACs prescription during the study period. Treatment patterns for OACs users will be evaluated for (1) continuous exposure to OACs: no treatment change until end of follow-up period, defined starting from the date of first prescription to the intended duration of that prescription, plus the duration of any overlapping and successive prescriptions of the same drug within 30 days after the expected end of a prescription. For VKAs, INR measurements if available will be treated as indicator for VKA exposure and therefore treated in the same way as prescriptions; (2) OACs discontinuation: no OACs prescription after a period of therapy without resumption of OACs; (3) OACs switch: this will include four switching categories: from antiplatelet only to OACs, from VKA to NOAC, from NOACs to VKA, and between NOACs switches. OACs not prescribed will be defined as no prescription record of an OACs at any time after NVAf diagnosis, this will also include patients prescribed lone antiplatelet therapy. Proportions of patients prescribed antiplatelets such as aspirin or other antiplatelets (i.e., clopidogrel, ticagrelor, or prasugrel) within the study period will be described for both OACs exposed and not exposed patients. Products codes of antiplatelet agents can be found in (Appendix 2).

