## 2. Phase 2 - Comparative study

**Exposures:** In this cohort, prescriptions for OAC will determine patient’s exposure status. NVAf patients identified from phase one and who have received a continuous prescription of either VKAs or NOACs within one year of NVAf diagnosis will be in the OACs “exposed group”. While “OACs unexposed” patients are individuals in phase one who haven’t received a prescription for anticoagulation therapy and remained OACs free for  $\geq 1$  year from NVAf diagnosis.

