**Outcomes:**

The primary outcomes include the reoccurrence of MB events or CRNMB for patients who did or did not continue OACs, the composite of stroke and other thromboembolic events, bleeding or cardiovascular related mortality, and all-cause mortality. Secondary outcome is the prescription of any OACs after the occurrence of the major bleeding events (VKAs or NOACs). We also aim to explore the timing of reinitiating OACs from the indexed bleeding event until the date of OACs prescription, and whether patients have continued on the same OAC before the index haemorrhage event, were switched to another agent after bleeding have occurred (i.e. from warfarin to any NOACs or from any NOACs to warfarin) or received lone antiplatelet therapy.

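### CRNMB can be met by stopping an OAC, a criterion open only to OAC users, which tilts the Phase 2 secondary and Phase 3 recurrent-bleeding comparisons against OAC

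*Protocol*

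**What the plan says.** The CRNMB definition appears twice. The section Outcomes to be measured describes bleeding "that did not satisfy the ISTH criteria and led to hospitalization, medical or surgical treatment, or led to discontinuation of OACs". The Phase 2 Outcomes paragraph repeats the criteria: "led to hospitalization, medical or surgical treatment, or led to discontinuation of OACs".

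The Phase 2 comparator consists of patients who have not "received a prescription for anticoagulation therapy and remained OACs free for" at least one year from diagnosis. They come from the Phase 1 classification, where "OACs not prescribed will be defined as no prescription record of an OACs at any time after NVAf diagnosis".

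The Phase 2 analysis (Data/statistical analysis) states that "Cox regression will be used to compute hazard ratios (HRs) of the outcomes of interest, comparing exposure to OACs versus no OACs". Against immortal time bias, the protocol will consider a time-varying exposure in which "the time period previous to the index date of OACs initiation is reclassified as nonuser".

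For Phase 3, "The primary outcomes include the reoccurrence of MB events or CRNMB for patients who did or did not continue OACs". That paragraph does not restate what CRNMB means, so the definition above is the only one in the document.

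**The concern.** A hazard ratio between two groups is interpretable only if the same clinical event counts, or fails to count, in the same way in both. Take a bleed that needed neither admission nor treatment. In a patient not on an OAC it can never be CRNMB. In a patient on an OAC the identical bleed becomes CRNMB if the drug is stopped because of it. OAC time has three routes to an event and non-OAC time has two.

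Two results are at stake:

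- the CRNMB part of the bleeding comparison under Aim 4 (Phase 2, secondary outcome);
- the bleeding-recurrence comparison under Aim 5 (Phase 3, listed among the primary outcomes), where patients who resumed an OAC can meet the extra criterion and patients who stayed off it cannot.

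In both, the tilt makes OAC look worse for bleeding.

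**Working it through.** The protocol gives no CRNMB rate, effect size or power, so there is no stated figure to reproduce. The check is first of logic, then of size under a stated assumption.

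**Step 1: which criteria each group can meet.**

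| Criterion | OAC time | Non-OAC time |
|---|---|---|
| Hospitalisation | yes | yes |
| Medical or surgical treatment | yes | yes |
| OAC discontinuation | yes | impossible |

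The comparator need only be OAC-free for the first year under the Phase 2 exposure definition, so a control could start and later stop an OAC. At that moment the patient is an OAC user, so the table still holds.

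**Step 2: does anything else in the protocol remove the asymmetry?**

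- There is no parallel criterion for non-users, such as stopping an antiplatelet, although the not-prescribed class includes patients on an antiplatelet alone.
- Propensity score matching, overlap weighting, covariate adjustment and E-values deal with confounding, not with an outcome defined through the exposure.
- Time-varying exposure moves pre-initiation time into the non-user category, where the third criterion is still impossible.
- No analysis without the criterion is stated, nor any restriction of it to comparisons among users.

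**Step 3: size for CRNMB alone.** Let r be the rate of bleeds that qualify by hospitalisation or treatment, equal in both groups, and d the rate of OAC-group bleeds that qualify only through discontinuation. Then s = d/(r + d), and

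apparent ratio = (r + d)/r = 1/(1 - s).

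| Assumed s | 1/(1 - s) |
|---|---|
| 5% | 1/0.95 = 1.05 |
| 10% | 1/0.90 = 1.11 |
| 20% | 1/0.80 = 1.25 |
| 30% | 1/0.70 = 1.43 |

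If the two-criterion rates differ by a true ratio T, the apparent ratio is T/(1 - s). The factor multiplies whatever the truth is.

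**Step 4: what drives s.** Suppose a share q of non-major bleeds is admitted or treated in both groups, and a share k of the remainder leads to stopping the OAC. The apparent ratio is (q + (1 - q)k)/q. Both q and k are assumptions.

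- q = 0.7, k = 0.1: (0.7 + 0.03)/0.7 = 1.04
- q = 0.5, k = 0.3: (0.5 + 0.15)/0.5 = 1.30

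The more broadly treatment is read, the larger q is and the smaller the bias.

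**Step 5: Phase 3 dilution.** If CRNMB makes up a share c of all major-or-CRNMB events in the resumed group, the discontinuation-only share of the pooled endpoint is cs, and the factor is 1/(1 - cs). This is below 1/(1 - s) whenever c is below 1. As an illustration, with c at one half and s at 20%, cs is 10% and the factor is 1/0.90 = 1.11 instead of 1.25. The planned time to the earliest of stroke, bleeding or death dilutes it further.

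**The case against.** **Continuous exposure.** Phase 2 admits to the exposed group patients with a continuous OAC prescription, and Phase 1 describes continuous exposure as unchanged until follow-up ends. If that meaning carried over, anyone stopping after a bleed would leave the exposed group and the third criterion would add little. This fails. Phase 3 is drawn from the same exposed group and expects some patients to stay off OAC after the index bleed, so the group must contain patients who stop.

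**Operation.** The protocol gives no rule tying a prescription gap to a preceding bleed, and outcomes are to be found through code lists that are not in view. The discontinuation criterion may be applied rarely, or an analysis plan may restrict it. This stands as a limit: the fault lies in a definition the protocol states, not in a bias shown in results.

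**Size.** The treatment criterion is broad and open to both groups, so s could be small. This stands, and the range above therefore starts at 5%.

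**Reach.** A reader might infer that the whole safety side of Aim 4 is compromised. It is not. The Phase 2 primary composite uses stroke, other thromboembolism and ISTH major bleeding, none of which depends on stopping an OAC.

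**Completeness of the remedy.** Decisions to admit or treat a bleed may themselves depend on whether the patient takes an OAC. Dropping the discontinuation criterion removes one structural asymmetry, not every one.

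**Conclusion.** The point holds. As written, CRNMB includes a criterion that only patients on an OAC can satisfy, and the protocol uses CRNMB in comparisons with patients who are not on one. The direction follows from the text: the criterion can only add OAC-side events. The size does not. The factor for CRNMB alone is 1.05 to 1.43 for s from 5% to 30%, where s is assumed and the two-criterion rates are taken as equal. It is smaller for the Phase 3 endpoint pooled with major bleeding, and it does not apply to the Phase 2 primary composite.

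Two stronger readings are not supported. One is that the CRNMB hazard ratio must exceed 1. That follows only if true rates are equal and s is above zero; the definition pushes the ratio upward but does not fix where it ends. The other is that the artefact would bolster the protocol's premise that bleeding risk on OAC is overestimated. An inflated bleeding ratio would do the reverse and appear to support clinicians' caution.

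This should be corrected before analysis. It affects a secondary outcome in Phase 2 and one component of a primary outcome in Phase 3.

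**What to change.** In Outcomes to be measured and in the Phase 2 Outcomes paragraph, state that for every exposed-versus-unexposed and resumed-versus-not-resumed comparison, CRNMB means a non-major bleed leading to hospitalisation or to medical or surgical treatment. State that the same definition governs the Phase 3 outcome. The Phase 3 paragraph holds no definition to reword, so a cross-reference is enough. Report bleeds that qualify only through OAC discontinuation descriptively, among OAC users.

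The cost is a wording change with no new data, and somewhat fewer CRNMB events in the OAC group. Any difference in admission or treatment decisions by OAC status remains and should be acknowledged as a limitation.
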